##### VIVE Pro Eye, HTC (High-Tech Computer) Corporation, New Taipei City, Taiwan

The VIVE Pro Eye is capable of delivering digitally rendered greenspace visual recordings from forested or park-like greenspaces. The headset has sensors that coordinate the virtual greenspace with the participants’ visual gaze (native eye tracking) to move the surroundings of the digital greenspace through interaction with the base stations using motion sensors mounted on tripods in front of the participant [89,90]. Set up will include downloading the VIVE and SteamVR software onto a computer specifically dedicated for the VIVE system (e.g., using Windows 10 operating system). Tracking will be performed on the computer software and saved for later review during data entry [91]. The computer will be located behind the chair in which the participant will be sitting. Sounds will be adjusted for those that are a part of the virtual greenspace; ambient sounds in the room will be muted. Although software comes with the purchase of the VIVE system, training videos can be found online and will be completed before use [87,88,89].

### 2.5. Baseline Fidelity Measures—Linkages to Equipment

Perception of air quality prior to introduction of phytoncides into the room’s air will be evaluated repeatedly prior to each intervention day using two healthy individuals of both assigned sexes each time to assess the air quality of the room at the set temperature of 70 °F while monitoring the relative humidity. We will use the facial exposure method as described by Fang, Clausen, and Fanger [92]. In order to ensure fidelity of the measures of phytoncide dose prior to, during, and at the end of the intervention period, the equipment mentioned above will be zero and span-calibrated before introduction of phytoncides into the room’s air. Recording temperature and humidity using the HOBO T/RH before and during the intervention will ensure that the reliability of the survey data from the P-Trak and the ppbRAE 3000 has not been affected by changes in temperature and humidity.

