### 2.2. Study Sample

The study sample for study #1 will be recruited from cancer patients with solid tumors (HR + HER2- breast, or prostate cancer) who have completed cancer therapy (hormone therapy excepted) as this population may benefit the most from increases in NK cell number and activity, perforin, and granulysin to prevent infection as patients become relatively immunocompromised after chemo- or radiation therapy. For study #2, the study sample will be recruited from axial spondyloarthritis patients who have chronic or breakthrough pain, as virtual reality has been shown to reduce pain, and d-limonene administration in animals has shown pain reduction. Since the two studies are set in the future and are pilot studies, we expect for study #1 to recruit and enroll 25 participants and for study #2 to recruit and enroll 25 participants. For study #1, the participant number is limited by budget and the cost of pre-clinical and clinical laboratory tests. For study #2, the participant number is limited by budget and the cost of paper-based tools. Concurrent controls for both studies will be identified by the clinicians in either the cancer clinics or the arthritis clinic. Concurrent controls will meet the same study inclusion and exclusion criteria as those who are enrolled in the study interventions. We expect to have 4 of each of the assigned genders in the control groups. The control groups will be randomized to receive neither SFIT intervention, VR, or atomized phytoncides. They will be exposed to atomized water dispersal for 1 h, the same length of time as the study participants who will receive the SFIT interventions. All the same data will be collected for both study #1 and study #2 on these control participants. At the end of the studies, should an effect of the SFIT intervention be noted, the control participants will have the opportunity to complete the same intervention. Clinicians will lead the recruitment of these patients, followed by a phone screening for inclusion and exclusion conducted by the principal investigator and research associate.

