### 2.4. Intervention—Procedure

Our two studies are novel as no one to date has used simulated forest immersion in patients with acute or chronic morbid conditions. The principal investigator (PI) and research associate (RA) will implement SFIT in a separate room from the room used to cross-check inclusion and exclusion, obtain informed consent, collect baseline measures, and allow the participant to rest. Prior to the arrival of the participant, the SFIT intervention space will be prepared. Preparation of the intervention space includes calibration of the instruments that will measure volatile organic compound particles (phytoncides are volatile organic compounds) and droplets, room temperature and humidity, and room surface temperatures, followed by measurement of the ambient particles and droplets and room temperature and humidity prior to the implementation of the atomized phytoncides [71,81]. Phytoncides α-pinene, β-pinene, and d-limonene (Floraplex Terpenes, Ypsilanti, MI, USA) will be prepared for atomization with a commercially available atomizer (Asakuki 500 mL Premium Atomizer, Tronhon Co., Ltd., Chongqing, China) that can emit phytoncides for up to 3 h. Once the dose expected (0.80 ppm) reaches the dose published by Li [6], the participant will be brought into the intervention room. To date, the Li study, which was conducted with healthy men, has been the only study to record phytoncide dose in a controlled setting. We will use this concentration as the target dose for our humidified phytoncide set up. Both at the beginning and at the end of 1 h of exposure to the simulated forest immersion therapy intervention, ambient phytoncide in the contained space will be measured indirectly by measuring both the increase in ambient air particle mass and number, as well as by measuring the change in total volatile organic compounds (VOCs). Total particle numbers will be measured with a continuous ultrafine particle counter (P-Trak 8525, TSI, Shoreview, MN, USA), and the total VOCs will be measured with the portable handheld monitor (Mini ppbRAE 3000, Honeywell International INC.; San Jose, CA, USA). The P-Trak and Mini ppbRAE 3000 will measure the increase in particle numbers and water droplets (aerosol), respectively, which will serve as a surrogate of relative exposure to phytoncide. Continuous monitoring of room temperature and relative humidity will be measured by the HOBO MX2301 Temperature/RH Data Logger (ONSET, Bourne, MA, USA). Room surface temperature will be measured by ADC Adtemp Mini 432 Non-Contact Infrared Thermometer (American Diagnostic Corporation, Hauppauge, NY, USA). VR will be provided by VIVE Pro Eye, HTC (high-tech computer) Corporation, (New Taipei City, Taiwan) with digital rendering of forested greenspace. Once 1 h of SFIT concludes, the participant will be removed to the preparation area and given instructions related to reporting unanticipated problems, adverse events, and serious adverse events, and an appointment to return for follow up on Day 3. See Figure 1, which illustrates the SFIT process/procedure.

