##### Measurement of Ambient Room Conditions

Room temperature and humidity may alter the overall measurement of particle number and droplets. Measuring all four of these ambient conditions will allow for consistency in the experimental condition between participants. The room has a set temperature of 70 °F, and since the room is located against a foundation wall, humidity may vary; therefore, it is important to monitor both of these ambient conditions and use cutoff criteria based on average temperature and humidity of the controlled lab setting. We will also use a non-contact infrared surface thermometer to measure radiant heat of room surfaces that may add to the perceived comfort of the SFIT intervention room [81]. The ADC Adtemp Mini 432 Non-Contact Infrared Thermometer (American Diagnostic Corporation, Hauppauge, NY, USA) with a range of 59–77 °F will be used for this purpose. The ambient room air temperature, humidity, and surface temperature date will be collected as a mean prior to, during, and at the end of the intervention.

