##### Asakuki 500 mL Premium Atomizer, Tronhon Co., Ltd., Chongqing, China

The atomizer holds 500 mL of liquid that can be atomized over 3 h. Of that 500 mL, a portion will be reduced that coincides with the amount of phytoncide that will be added. We expect that we will add 30 mL per phytoncide to the atomizer to achieve the detectable published amount [6,21]. Mist will be created by an ultrasonic plate within the atomizer, and the mist will be adjusted for a weak mist or a strong mist. Choice of weak or strong mist will be adjusted to fit the published detectable amount of phytoncide. Mist time can be regulated to maintain 60, 120, and 180 min of operation. We will use a 60 min mist time with the participants of study #1 and study #2. A fan within the atomizer will disperse the mist into the room. Room temperature and humidity will be monitored continuously as low temperature and high humidity may condense the mist into water droplets [87], which is to be avoided to allow for accurate dose calculations.

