#### Feasibility and Reliability of Intervention Stability

We expect to determine the ease of use of VR and phytoncide atomization, the drop off of phytoncide over the intervention period, and engagement in VR leading to a standardization of the procedure and protocol. Data will be collected from the participant, and the research associate and principal investigator will use field notes and will include challenges and facilitators related to the delivery method of VR and phytoncides and the ability of the participant to engage in VR for the duration of the study intervention. Atomized phytoncides prior to and after 1 h of dose delivery will be used to measure by the P-trak and the Mini ppbRAE3000 to determine dose drop off during the intervention delivery. Quantitative data related to dose drop off will be analyzed by *t*-test with an α level of 0.05. We will collect deviations from the standardized procedures, including the deployment of VR and atomized phytoncides. We will monitor the timing, preservation, and delivery of specimens to specialized labs on the academic healthcare campus in order to track the ability to maintain the expected optimized rigor in testing immune cells.

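### Logging temperature and humidity cannot ensure that the dose readings are unaffected, and the start-to-end drop-off test can mix water mist and humidity with phytoncide change

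*Protocol article*

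**What the plan says.** The assurance is in section 2.5. The HOBO logger's record, kept ahead of and throughout the session, is said to "ensure that the reliability of the survey data from the P-Trak and the ppbRAE 3000 has not been affected by changes in temperature"; the sentence goes on to name humidity as well.

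The other statements that bear on it are these:

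- Measurement of Ambient Room Conditions: "Room temperature and humidity may alter the overall measurement of particle number and droplets". The same section sets the temperature, says that humidity may vary, and mentions cutoff criteria for both without giving a value. Section 3.1 lists cutoff criteria among the things the studies are expected to produce.
- Section 2.4, on the surrogate: the P-Trak and ppbRAE "will measure the increase in particle numbers and water droplets (aerosol), respectively, which will serve as a surrogate of relative exposure to phytoncide".
- Section 2.4, on timing: "Both at the beginning and at the end of 1 h of exposure to the simulated forest immersion therapy intervention, ambient phytoncide" is measured indirectly. The participant enters after a pre-charge: "Once the dose expected (0.80 ppm) reaches the dose published". Its length is not given.
- Atomizer section: "We will use a 60 min mist time with the participants of study #1 and study #2". The reservoir holds 500 mL, with an expected 30 mL per phytoncide. Condensation is to be avoided, and the step given for this is monitoring.
- Feasibility and Reliability of Intervention Stability: "Quantitative data related to dose drop off will be analyzed by" a t-test at an α of 0.05.
- Section 2.2: controls receive one hour of atomized water, and "All the same data will be collected for both study #1 and study #2 on these control participants".

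**The concern.** A logger shows whether conditions changed. It does not stop the change from reaching the other two instruments, and no limit, correction or action is attached to the log. The likely source of humidity is the intervention itself, since the atomizer releases mostly water during the interval that the drop-off test spans. The surrogate also counts water droplets, so even at steady humidity a change in water aerosol could be read as a change in phytoncide.

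The drop-off comparison is the only analysis in the article with a named test and an α level. It also feeds the guidance on keeping the dose consistent that section 3.1 promises. If a water or humidity effect is taken for phytoncide change, a stable dose could be reported as falling, or a falling dose as stable. The control sessions could help separate the two, but the article does not give them this role.

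**Working it through.** The article gives no figure for this effect, so there is none to reproduce. Three checks follow.

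**1. How much could humidity rise between the two readings?**

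Inputs from the article: room 20 × 15 × 12 ft (section 2.3); 70 °F (ambient conditions section); 500 mL atomized over 3 h and 30 mL per phytoncide (atomizer section); logger accuracy ±3.5% RH (HOBO section). Saturation vapour density at 21.1 °C is 18.4 g/m³ by the Magnus formula.

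- Volume: 3,600 ft³ × 0.02832 = 101.9 m³. Vapour at saturation: 101.9 × 18.4 ≈ 1,875 g.
- Output: 500 / 3 = 166.7 mL/h.
- Water share: (500 − 90) / 500 = 0.82 with three phytoncides; (500 − 30) / 500 = 0.94 with d-limonene alone.
- Water in 60 min: 166.7 × 0.82 = 137 g; 166.7 × 0.94 = 157 g.
- Closed room: 137 / 1,875 = 7.3 RH points; 157 / 1,875 = 8.4 RH points.

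With N air changes per hour, a pre-charge of p hours and perfect mixing, the rise over the exposure hour is the closed-room rise × e^(−Np) × (1 − e^(−N)) / N. N and p are not in the article, so they are varied here as assumptions. For the three-phytoncide mix, in RH points:

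| Air changes per hour | p = 0 | p = 0.25 h | p = 0.5 h | p = 1 h |
|---|---|---|---|---|
| 0 | 7.3 | 7.3 | 7.3 | 7.3 |
| 0.5 | 5.7 | 5.1 | 4.5 | 3.5 |
| 1 | 4.6 | 3.6 | 2.8 | 1.7 |
| 2 | 3.2 | 1.9 | 1.2 | 0.4 |
| 4 | 1.8 | 0.7 | 0.2 | 0.0 |
| 6 | 1.2 | 0.3 | 0.1 | 0.0 |

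The rise clearly exceeds the logger's ±3.5% only when air exchange is low. The table assumes that mist runs through the whole exposure hour at the 3 h rate; the article leaves the choice of weak or strong mist open.

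**2. What would an instrument shift do to the t-test?**

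The article gives no instrument variance and no response to humidity, so the shift is expressed in SDs of the start-to-end difference, as an assumption. For a paired two-sided test at 0.05 with n = 25, the noncentrality is shift × √25.

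| Shift (SD) | Rejection rate with no true change | Power when the shift offsets a true 0.6 SD drop |
|---|---|---|
| 0 | 5.0% | 82% |
| 0.1 | 7.7% | 67% |
| 0.2 | 16% | 48% |
| 0.3 | 30% | 30% |
| 0.5 | 67% | 7.7% |

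These figures show how sensitive the test is. They do not estimate the actual bias.

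**3. What would a control reference cost in precision?**

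The relative standard error of an SFIT-minus-control difference, against the SFIT change alone and with equal variances, is √(1/n₁ + 1/n₀) / √(1/n₁). Section 2.2 expects 4 controls of each gender, read here as 8 per study.

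- 25 SFIT and 8 control sessions: 0.406 / 0.200 = 2.0.
- 17 and 8, if the 25 include the controls: 0.429 / 0.243 = 1.8.

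**The case against.** The plan has some handling of its own. Humidity is monitored continuously, cutoff criteria are mentioned, and the assurance can be read charitably as saying that the log will verify that readings were unaffected. This stands in part. The cutoffs carry no value, are presented as a way to keep conditions alike between participants, and are listed as a study output. They would not remove a shift within a session.

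A second objection is that a journal article need not list covariates or reference comparisons. That is fair, and their absence is not the finding. The finding is the positive claim in section 2.5, set against the article's own account of the surrogate and the mist.

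Third, the humidity rise may be small. The start reading follows a pre-charge that has already humidified the room, and with ventilation the later rise can fall within logger accuracy. This stands, as the first table shows.

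A reader might go further and infer that the error has the same direction in every session, or that the drop-off result is biased by a known amount. The documents do not support either. They allow a rise in humidity to be calculated, but nothing states how either instrument responds to it.

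**Conclusion.** The point holds in a limited form. Section 2.5 claims a protection that logging cannot give, while another section of the same article concedes the effect. Because the surrogate includes water droplets and a mainly water mist runs between the readings, the start-to-end t-test cannot by itself attribute a change to phytoncide.

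The humidity rise lies between almost nothing and about 7 to 8 RH points, depending on ventilation, pre-charge time and mist setting. The resulting instrument error is unknown in size and sign. This affects a feasibility measure in a budget-limited pilot. It deserves correction because the drop-off result is meant to inform how a consistent dose is maintained, and the means to examine it are already in the design.

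**What to change.** In section 2.5, say that the temperature and humidity record *will be used to check, and where needed adjust for,* effects on the P-Trak and ppbRAE readings.

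In the feasibility section, keep the start-to-end comparison in SFIT sessions and report VOC (ppbRAE) and particle count (P-Trak) separately. Section 2.4 gives the ppbRAE both total VOCs and water droplets, while the section on that instrument gives it VOCs; these should be reconciled first. Then add:

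- the same start-to-end change in the water-mist control sessions, with the SFIT-minus-control difference and its confidence interval;
- a sensitivity analysis with the logged change in relative humidity and temperature as covariates.

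Call the change phytoncide drop-off only if it is not matched in the control sessions.

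This is mainly a change of wording and analysis and, on the statement in section 2.2, needs no new outcome data. It has three costs. With 8 controls per study, the difference has about 1.8 to 2 times the standard error of the SFIT change alone, so it should supplement that comparison and not replace it. Subtraction removes only additive shifts. It also relies on comparable mist output and timing in control sessions, which should be recorded: these sessions have no phytoncide target to mark entry, and at the same output they release more water (167 g against 137 g or 157 g in an hour).

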#### Feasibility and Reliability of Intervention Stability

We expect to determine the ease of use of VR and phytoncide atomization, the drop off of phytoncide over the intervention period, and engagement in VR leading to a standardization of the procedure and protocol. Data will be collected from the participant, and the research associate and principal investigator will use field notes and will include challenges and facilitators related to the delivery method of VR and phytoncides and the ability of the participant to engage in VR for the duration of the study intervention. Atomized phytoncides prior to and after 1 h of dose delivery will be used to measure by the P-trak and the Mini ppbRAE3000 to determine dose drop off during the intervention delivery. Quantitative data related to dose drop off will be analyzed by *t*-test with an α level of 0.05. We will collect deviations from the standardized procedures, including the deployment of VR and atomized phytoncides. We will monitor the timing, preservation, and delivery of specimens to specialized labs on the academic healthcare campus in order to track the ability to maintain the expected optimized rigor in testing immune cells.

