##### Mini ppbRAE 3000, Honeywell International Inc., San Jose, CA, USA

The ppbRAE 3000 measures volatile organic compounds (VOCs) related to the phytoncides that we are atomizing. The ppbRAE 3000 will be zero-calibrated using a charcoal zero filter and Isobutylene Air Balanced span gas [84]. For two-point calibration, isobutylene at 10 ppm and 100 ppm will be used [85]. During two-point calibration, we will use a set 0.5 LPM regulator. This regulator can handle up to 500 psi, which is the psi of the span gas cylinders and also within the toleration limit of the ppbRAE 3000 regarding pressure and flow. It is important that the gas cylinder connection is CGA 600 and corresponds to the connection on the regulator, meaning that the threading has to be compatible between the cylinder and the regulator. If 500psi is exceeded during calibration or survey mode, the diaphragm within the RAE 3000 may be damaged, leading to inaccurate data collection. In survey mode, data will be updated every 60 s and a data log will be created. The data log will be downloaded using software specific to the ppbRAE 3000 and found online [82].

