### 3.1. Expected Outcomes

The expected outcome for the future two studies is the creation of a standardized protocol for deploying SFIT. This will include calibration and measurement set points, cutoff criteria and describing how to maintain a consistent dose of phytoncide and ease the use of VR for participants. We expect to uncover pertinent adverse events, severe adverse events, and unanticipated problems. For study #1, we expect that the combined use of our three phytoncides of interest and VR will improve NK cell numbers and activity and blood levels of perforin and granulysin in patients with breast or prostate cancer. For study #2, we expect that the use of d-limonene and VR will reduce pain, stress, and depression in patients with axial spondyloarthritis.

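### The t-test set for dose drop-off does not answer whether the phytoncide dose stays consistent; an interval estimate judged against a pre-set acceptable loss would

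*Protocol article*

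**What the plan says.** The subsection Feasibility and Reliability of Intervention Stability, under Section 2.5, sets out to determine, among other things, "the drop off of phytoncide over the intervention period, and engagement in VR leading to a standardization of the procedure and protocol". Its dose data come from two time points: "Atomized phytoncides prior to and after 1 h of dose delivery will be used to measure by the P-trak and the Mini ppbRAE3000". The analysis follows: "Quantitative data related to dose drop off will be analyzed by" t-test "with an α level of 0.05". This is the only analysis of drop-off that the article states, and it names no acceptable loss.

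Section 2.4 confirms the two time points, with ambient phytoncide measured "Both at the beginning and at the end of 1 h of exposure to the simulated forest immersion therapy intervention". Section 3.1 lists cutoff criteria among the expected products, together with "describing how to maintain a consistent dose of phytoncide". Richer data will exist. For the VOC monitor, Section 2.4.1 says that "data will be updated every 60 s and a data log will be created", and the particle counter's log also refreshes once a minute.

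**The concern.** The t-test takes zero mean change from start to end as its null hypothesis. The practical question is whether the loss over the hour is small enough for the dose to count as consistent. The p-value does not answer this in either direction:

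- If it is above 0.05, the data may still be compatible with a loss that matters. How large depends on the number of sessions and the spread of the changes.
- If it is below 0.05, the loss may still be too small to matter.

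The named test also uses two readings per session, although about 60 per instrument will be logged.

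A standardized procedure with a consistent dose is a main product of the two pilots, and the Discussion plans later designs on it. A bare test result would tell those designs little about how much dose is lost or how much sessions differ.

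**Working it through.** The article gives no power, SD, margin or sample-size figure for this test, so there is nothing of its own to reproduce. The check asks what a t-test result could tell the investigators.

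**Inputs**
- Two-sided α of 0.05. The α is stated; two-sided is assumed.
- Sessions per study: 25 enrolled (Section 2.2). Controls receive atomized water only and number 4 × 2 = 8. It is unclear whether they fall within the 25, so phytoncide sessions number 25 − 8 = 17, or 25.
- Target dose: 0.80 ppm (Section 2.4).
- SD of the within-session change: not given. **Assumed** to be 10% to 50% of the starting dose.
- Paired analysis is assumed, because start and end come from the same session.

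**Step 1: largest loss compatible with a non-significant result.** The 95% half-width is h = t(0.975, n−1) × SD/√n. A just non-significant result has a mean loss of h, so its upper limit is 2h.

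For n = 17 and SD 10%: h = 2.120 × 10%/√17 = 5.1%, so 2h = 10%. For n = 25 and SD 10%: h = 2.064 × 10%/5 = 4.1%, so 2h = 8%.

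| SD of change (% of starting dose) | 10 | 20 | 30 | 40 | 50 |
|---|---|---|---|---|---|
| Largest compatible loss, n = 17 (%) | 10 | 21 | 31 | 41 | 51 |
| Largest compatible loss, n = 25 (%) | 8 | 17 | 25 | 33 | 41 |

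On the 0.80 ppm target, a 41% loss is 0.41 × 0.80 = 0.33 ppm.

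**Step 2: smallest loss that becomes significant.** This is h itself. With n = 25 and SD 10% it is 4.1% of the starting dose, or 0.041 × 0.80 = 0.033 ppm.

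**Step 3: power for a true mean loss of 20%.** Noncentral t, n−1 degrees of freedom, noncentrality (20%/SD) × √n.

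| SD of change (%) | 20 | 30 | 40 | 50 |
|---|---|---|---|---|
| Power, n = 17 (%) | 97 | 73 | 49 | 34 |
| Power, n = 25 (%) | >99 | 89 | 67 | 48 |

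**Step 4: would an interval rule be workable?** The documents give no margin, so 20% of the starting dose serves here **as illustration only**. The entries are the simulated chance that the upper one-sided 95% limit for the loss falls below 20%.

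| SD of change (%) | 20 | 30 | 40 | 50 |
|---|---|---|---|---|
| True loss 0, n = 17 (%) | 99 | 84 | 63 | 48 |
| True loss 0, n = 25 (%) | >99 | 95 | 79 | 62 |
| True loss 10%, n = 17 (%) | 63 | 37 | 26 | 20 |
| True loss 10%, n = 25 (%) | 79 | 49 | 33 | 25 |

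The rule works well with moderately precise readings and becomes demanding with noisy ones. A margin that also limited a rise in dose would be harder to meet.

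**The case against.** The best defence is that the article states no decision rule. It says that drop-off will be determined, and a difference test fits the literal question of whether the dose falls over the hour. A reader might infer that a non-significant result will be taken as proof of a stable dose. The article nowhere says so; that reading rests only on the subsection heading and the stated purpose. This stands. What remains is that the one analysis named does not answer the question of consistency.

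A reader might also infer that a rise and fall within the hour would go unseen. That goes too far. Both instruments log every minute, the logs are downloaded, and Section 2.5 speaks of dose measures during the session. Only the named test leaves those readings out.

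Nor can one say that a large loss is necessarily compatible with non-significance. With an SD of 10% the compatible loss is only 8% to 10%; it reaches 25% to 51% when the SD is 30% to 50%.

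Finally, the article does not say whether the test is paired. Taken alone this is minor, since a condensed article may leave it to a fuller document. Pairing may also matter less here, because the participant enters only once the target concentration is reached, which should hold start readings close together.

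**Conclusion.** The point holds in a limited form. The article fixes a test of no change as its only analysis of dose drop-off, and that test can neither show a consistent dose nor separate a trivial loss from an important one.

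How much this matters depends on an SD that the documents do not give. Over the assumed range, a just non-significant paired test leaves room for a loss of 10% to 51% of the starting dose with 17 sessions and 8% to 41% with 25. These figures also assume two-sided testing and separate analysis of each study, which is sensible because the phytoncide mixes differ.

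This is a cheap improvement, held with moderate confidence. The documents do not support a claim that the investigators will misread the test.

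**What to change.** Replace the t-test sentence with an estimation plan:

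1. For each session, compute the paired start-to-end change in ppm and as a percentage of the starting value, and the time-weighted mean over the hour from the minute-by-minute VOC log.
2. Report the mean change with its confidence interval, the between-session SD, and the profile within the hour.
3. Set an acceptable-loss margin before the first session, and conclude that the dose is stable only if the confidence interval lies within it. The margin is for the investigators to choose; the 20% used in the working is not a recommendation.

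The cost is a change of analysis wording, since the readings are already to be logged. The downside is that with noisy readings the conclusion may be that stability was not shown, even when the true loss is small. That would be a fair account of what the data can support, and the SD obtained would help in planning the next study.
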